### Exclusion criteria

2.4

*Systemic diseases*: Patients with severe psychiatric disorders, severe cardiovascular or cerebrovascular diseases, hepatic or renal dysfunction, digestive dysfunction, coagulation disorders, or other severe systemic diseases.

*Medical history*: Individuals with a history of gastrointestinal surgery, psychiatric disorders, alcohol abuse, or drug abuse. Patients with overlapping syndromes such as Gastroesophageal Reflux Disease (GERD) or Irritable Bowel Syndrome (IBS), or those with current *Helicobacter pylori* infection.

*Systemic or environmental factors*: Patients experiencing insomnia or dyspepsia caused by systemic conditions such as pain, fever, cough, surgery, trauma, or external environmental factors.

*Ear skin conditions*: Patients with skin conditions in the ear stimulation area that may affect conductivity, including allergies, abrasions, ulcers, edema, neoplasms, scars, inflammation, or papules.

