### Randomization and blinding

2.6

The randomized controlled trial (RCT) utilized a simple randomization method implemented via the PROC PLAN procedure in SAS 9.4 software, which was designed by an independent statistician. A fixed seed number of 60 was preset to ensure reproducibility, and participants were allocated to the two groups (30 each) at a 1:1 ratio, with random numbering from 01 to 60, generating 60 unique sequences to ensure unbiased group allocation. The group allocation information was sealed in tamper-evident opaque envelopes and managed by a blinded study coordinator who was not involved in participant recruitment or outcome assessment, ensuring strict allocation concealment.

During trial execution, consecutively enrolled participants meeting inclusion criteria were sequentially assigned unique identification numbers. The blinded trial coordinator strictly adhered to the enrollment chronology when unsealing pre-sequenced, tamper-evident sealed envelopes. The revealed allocation information was subsequently transferred to an independent investigator uninvolved in recruitment or intervention delivery, who executed group assignments per the predefined randomization matrix. The study protocol explicitly prohibited any deviation from allocation sequences or non-programmatic modifications.

The independent researcher, based on randomized allocation, preset the transcutaneous auricular vagus nerve stimulator (tVNS501) with fixed parameters (intensity: 20–40 mA, frequency: 80 Hz, pulse width: 100 μs, pulse 40–60s) and blinded the display screen using opaque tape before handing it to a clinical operator. In the active stimulation group, the device was powered to deliver real stimulation, while in the sham stimulation group, the device remained inactive (no current output) but maintained physical contact. A triple-blind design (participant-operator-outcome assessor) was implemented throughout the study to maintain blinding of group assignment (taVNS or sham taVNS). Unblinding was performed post-database lock by an independent statistician using SAS 9.4 (SAS Institute Inc., Cary, NC), strictly adhering to the predefined protocol. This study strictly adhered to the principle of observer independence in clinical research (Figure 1).

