### Intervention

2.7

Following standardized screening, all participating clinicians underwent unified training in both taVNS and sham taVNS protocols. The informed consent form explicitly stated that the study involved two distinct neuromodulation interventions (which may differ in electrical sensation and therapeutic responses). Training modules included: (1) Device operation: standardized procedures for power cycling and locked parameter interfaces; (2) Anatomical localization: precise electrode placement at the tragus: the inferior margin of the intersection between the superior and inferior crura of the antihelix within the cymba conchae and the junction of the inferior crus of the antihelix and the auricle within the cymba conchae using auricular anatomical charts; (3) Blinding maintenance: standardized communication protocols to prevent unintentional disclosure of group allocation. All interventions were conducted in standardized treatment rooms within the hospital inpatient department.

All clinicians participating in this study were required to have at least 2 years of standardized acupuncture practice. Participants were placed in a supine position, and the auricular stimulation areas were cleaned with 75% ethanol solution followed by placement of ear clips. The clinically trained operator, blinded to group assignment, using transcutaneous auricular vagus nerve stimulators (tVNS501), precisely placed bipolar electrodes at standardized anatomical sites: the concha cymba (the inferior margin of the intersection between the superior and inferior crura of the antihelix within the cymba conchae). The intervention protocol consisted of 30-min sessions, administered weekdays from 9:00 to 11:00 AM for three consecutive weeks (15 sessions total).

Participants shall be withdrawn from the trial and provided with appropriate medical interventions under any of the following circumstances: (1) occurrence of serious adverse events; (2) voluntary withdrawal request from the participant; (3) clinical deterioration of the underlying condition; (4) requirement for prioritized treatment of other medical disorders; or (5) development of localized irritation or allergic reactions.

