### Data safety monitoring protocol

2.10

An independent Data Safety Monitoring Board (DSMB) was established, comprising clinical specialists, biostatisticians, methodological experts, and ethicists (all members provided signed conflict-of-interest declarations). The DSMB conducts dynamic safety surveillance through scheduled 24-week meetings and emergency sessions triggered by predefined thresholds (e.g., >10% SAE incidence at any site or > 20% participant dropout rate).

Adverse events were classified into four tiers per CTCAE v5.0 criteria: Grade 1 (asymptomatic/mild symptoms requiring monitoring), Grade 2 (interruption of intervention ≤7 days with symptomatic treatment), Grade 3 (intervention termination and multidisciplinary consultation), and Grade 4 (immediate emergency care and permanent withdrawal).

All SAEs were reported within 12 h (life-threatening) to 24 h (non-critical). Full compliance with Council for International Organizations of Medical Sciences (CIOMS) VI standards for Suspected Unexpected Serious Adverse Reaction (SUSAR) reporting was maintained, with critical protocol amendments requiring ≥75% approval via anonymous voting.

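### A Grade 2 ear reaction means withdrawal from the trial under 2.7(5) but only a pause under 2.10, and no precedence is stated

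*Protocol article*

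**What the plan says.** **Withdrawal rule (2.7 Intervention).** The lead-in is mandatory and concerns the trial, not only the treatment: "Participants shall be withdrawn from the trial and provided with appropriate medical interventions under any of the following circumstances". The last listed circumstance is "5) development of localized irritation or allergic reactions". It carries no grade threshold.

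**Graded actions (2.10 Data safety monitoring protocol).** For adverse events in general, with no exception for the ear site:

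- "Grade 1 (asymptomatic/mild symptoms requiring monitoring")
- "Grade 2 (interruption of intervention ≤7 days with symptomatic treatment")
- "Grade 3 (intervention termination and multidisciplinary consultation")
- "Grade 4 (immediate emergency care and permanent withdrawal")

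**Related text.**

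- Section 2.4 excludes at entry "Patients with skin conditions in the ear stimulation area that may affect conductivity, including allergies, abrasions, ulcers, edema, neoplasms, scars, inflammation, or papules".
- Section 2.6 says of the sham arm that "the device remained inactive (no current output) but maintained physical contact".
- Section 2.8.5 limits the primary (ITT) set to participants with at least one session, a baseline assessment and at least one evaluation after baseline. It keeps participants who discontinue for adverse events in a modified per-protocol set, for safety only.
- PSQI and NDSI are scheduled at baseline, at T1 (week 3) and at T2 (follow-up after treatment).

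**The concern.** An investigator facing a Grade 2 skin reaction under the electrode cannot both remove the participant from the trial and pause stimulation for up to a week with a view to resuming. Neither section cites the other, exempts local reactions or gives an order of precedence, so two investigators could handle the same event differently and both be following the protocol.

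The second issue is what withdrawal from the trial does to the data. The first scheduled efficacy assessment after baseline is T1. A participant removed earlier has no post-baseline evaluation unless one is taken at withdrawal, and the article does not say whether it is. Without one, that participant is outside the primary set, and multiple imputation applied to that set does not bring the participant back. The exclusion would follow from an event that the stimulation itself may have caused. This is the kind of post-randomization loss that an intention-to-treat analysis is meant to avoid.

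**Working it through.** **Step 1. The two rules side by side, for a reaction at the ear.**

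| Grade | 2.7(5) | 2.10 | Compatible? |
|---|---|---|---|
| 1 | withdraw from trial | monitor | Not strictly contradictory: a withdrawn person can still be monitored |
| 2 | withdraw from trial | pause up to 7 days, treat symptoms | No |
| 3 | withdraw from trial | end the intervention | Both stop stimulation; they differ on whether trial participation ends |
| 4 | withdraw from trial | emergency care, permanent withdrawal | Yes |

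The strict conflict is at Grade 2.

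**Step 2. Route out of the primary analysis.** Four conditions must all hold: a local reaction occurs; 2.7(5) is the rule applied; it is applied before T1; no evaluation is taken at withdrawal. The participant then fails the post-baseline requirement in 2.8.5.

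**Step 3. Illustration of size.** The plan gives no figure for this point to reproduce, and no irritation rate. The inputs, all from 2.5, are 30 per group, response rates of 70% (active) and 20% (sham), and 5–10% anticipated dropout. The dropout figure covers all causes. It is borrowed here as an upper limit for f, the fraction of the active arm lost by this route, with no offsetting loss in the sham arm.

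- Number lost: 30 × f = 30 × 0.05 to 30 × 0.10 = 1.5 to 3 participants.
- If those lost would have responded like completers, the overstatement is 0 points.
- If those lost would have responded like sham, the true active rate with everyone kept is 0.70(1 − f) + 0.20f:
  - f = 0.05: 0.665 + 0.010 = 0.675, overstated by 2.5 points.
  - f = 0.10: 0.630 + 0.020 = 0.650, overstated by 5 points.
- Planned difference: 70 − 20 = 50 points.

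**Step 4. Power.** Two-proportion z-test with pooled null variance, two-sided alpha 0.05: power = Φ[(0.50 − 1.96·s0)/s1], where s0 is the pooled standard error and s1 the unpooled one.

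- 30 vs 30: s0 = 0.1285, s1 = 0.1111; (0.50 − 0.2518)/0.1111 = 2.24; power 98.7%.
- 27 vs 30: s0 = 0.1316, s1 = 0.1145; (0.50 − 0.2579)/0.1145 = 2.11; power 98.3%.

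Power is not the issue. The effect on mean change in PSQI or NDSI, the stated primary endpoints, cannot be computed because the article gives no means or standard deviations.

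**Step 5. Dose after a Grade 2 pause.** A 7-day pause covers up to 5 weekday sessions. If they are not made up, 10/15 = 66.7% of the dose is delivered, below the 80% per-protocol limit (12/15). Pausing and resuming therefore has its own cost.

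**The case against.** **The specific rule prevails.** A rule naming one event type ordinarily overrides general tiers, and the ear-skin exclusion in 2.4 points the same way. Stopping early for local reactions is also a cautious choice in patients aged 60–85. This is a fair reading, and it would reduce the conflict to a missing cross-reference. But the protocol does not say so. Moreover, 2.4 is about conductivity: it supports stopping stimulation on affected skin and gives no reason to stop collecting questionnaires.

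**The loss comes from the ITT definition and from silence.** Largely true. The post-baseline requirement affects every withdrawal before T1, whatever its reason. An evaluation at withdrawal may be specified in the full protocol, which is not shown, so its absence from the article is not itself a fault. What 2.7(5) adds is that a mild event, possibly caused by treatment, is enough to start the process.

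**Readings that go too far.**

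- A reader might infer that Grade 1 is an equally hard contradiction. It is not (step 1).
- A reader might infer that the active arm will lose more participants because only it receives current. That is plausible, but sham devices also touch the skin and no rates are given for either arm.
- A reader might infer that 2.7(5) must give way to pausing by grade. The documents do not settle this: step 5 shows what pausing does to dose, and resuming on irritated skin sits awkwardly with 2.4.
- Section 2.9.3 labels Grades 1–2 as needing no intervention, which does not fit the Grade 2 action in 2.10. That is a clerical mismatch in a reporting stratum and adds nothing of substance.

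**Conclusion.** The point holds at Grade 2: 2.7(5) and 2.10 prescribe incompatible actions for a local ear reaction, and no text decides between them. This rests on the wording alone.

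The analysis consequence is conditional. If 2.7(5) is followed before T1 and no evaluation is taken at withdrawal, a randomized participant leaves the efficacy comparison because of a mild, possibly treatment-related event. The size is unknown and probably small. The range of 0 to 5 points against a planned 50 is an illustration. Its upper end needs the whole 10% dropout allowance to be ear reactions in the active arm, all before T1, none evaluated, all responding like sham, and no matching loss in the sham arm. The documents do not support a claim of material bias or of lost power. The correction is worth making because the conflict is plain and the remedy is cheap.

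**What to change.** 1. **Section 2.7(5):** reword it from withdrawal from the trial to stopping stimulation. The sponsor may keep the stricter stop at any grade for ear-site reactions.
2. **Section 2.10:** if that stricter stop is kept, state that it takes precedence over the general grades for reactions at the stimulation site.
3. **Sections 2.7 and 2.8.5:** state that participants whose stimulation is stopped for an adverse event still complete PSQI and NDSI at T1 and T2 and stay in the primary analysis unless they withdraw consent.

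**Cost.** A protocol amendment touching 2.7, 2.8.5 and 2.10. Section 2.1 records first enrolment in July 2024, so this is a change to a running trial, and 2.10 requires at least 75% approval if it counts as a critical amendment. A few participants would be followed off treatment, with questionnaires already on the schedule. Participant safety is not reduced, because stimulation can still stop at once on affected skin.

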### Quality control and assurance

2.11

#### Selection bias risks

2.11.1

To mitigate selection bias risks, this study implemented a rigorously designed RCT framework. Participants were stratified based on key baseline characteristics (e.g., age, disease severity) and subsequently allocated to intervention or control groups via computer-generated randomization sequences. This dual strategy of stratification and randomization ensured balanced distribution of confounding variables across study arms, thereby minimizing systematic differences between groups.

An independent statistician executed the randomization process to eliminate investigator interference in group assignment, while allocation concealment was maintained until participant enrollment to prevent selection bias arising from foreknowledge of treatment assignments. These measures collectively ensured inter-group comparability and mitigated potential biases associated with non-random allocation or investigator-driven participant selection.

#### Control of confounding bias

2.11.2

Confounding bias predominantly arises during data analysis due to distorted causal relationships between exposure factors and outcome variables. When confounding factors (third variables associated with both exposure and outcome) remain inadequately adjusted, erroneous causal attribution may occur, leading to overestimation or underestimation of effect sizes. This study implemented multivariable regression models (adjusting for baseline covariates such as age and gender) combined with propensity score matching to statistically control known confounders.

Additionally, sensitivity analyses were conducted to assess potential impacts of unmeasured confounders, with *E*-values quantifying the robustness of causal inferences. A prospective covariate data collection protocol (based on literature review and causal diagram analysis) further ensured systematic identification of confounding factors.

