### Sample size estimation

2.5

Based on existing RCT literature, the efficacy rate of taVNS in treating elderly patients with CI ranges from 73.3 to 93.3% (21, 22), while its efficacy in FD reaches 92.3% (3). Building upon our preliminary exploratory clinical study involving 10 cases, we observed an 80.0% efficacy rate (*p* < 0.01) for taVNS in treating elderly patients with CI comorbid with FD, demonstrating significant clinical effectiveness.

This study employed a superiority trial design and utilized PASS 2021 software (NCSS LLC, Kaysville, USA) for prospective sample size estimation. Based on clinical data reported in reference (23), with anticipated efficacy rates of 20% in the sham stimulation group and 70% in the active stimulation group, we conducted a two-independent proportion *z*-test analysis with the following parameters: type I error probability *α* = 0.05, statistical power 1-*β* = 0.99, and 1:1 allocation ratio. Through Monte Carlo simulation validation, the minimum theoretical sample size was calculated as 28 participants per group.

In accordance with CONSORT Statement guidelines regarding dropout rates and considering our institutional clinical practice experience with anticipated 5–10% dropout rates, we ultimately determined to enroll 30 participants per group (total *N* = 60). This sample size enables detection of a Cohen’s *h* effect size of 0.99 (Power = 0.991, 95% CI 0.89–1.07), satisfying the statistical power requirements for superiority trials.

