##### Neurotransmitter metabolomics profiling

2.8.3.4

Assessment timepoints: Consistent with the aforementioned schedule (T0-T1).

Analytical platform: Separation was performed using an Agilent 1,290 Infinity LC system coupled with a 5,500 QTRAP mass spectrometer (SCIEX) operated in negative ion mode.

Blood sampling protocol: Venous blood samples were collected at T0 (baseline) and T1 (post-intervention) under morning fasting conditions (≥8 h overnight fast).

Analytes:

Monoamines: DA, 5-HT, NE.Amino acids: Glu, GABA.

Interpretation criteria: Pearson correlation analysis was performed to assess the association between dynamic changes in neurotransmitter levels and improvement magnitudes of PSQI/NDSI scores, with |*r*| ≥ 0.3 defined as significant correlation (two-tailed test, *p* < 0.05).

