#### Design of the protocol

2.11.3

This study employed a prospective randomized double-blind RCT design, validated against international CONSORT guidelines. The randomization process is implemented through a computer-generated block randomization sequences. Participant allocation was executed by an independent statistician through an Interactive Web Response System (IWRS), ensuring allocation concealment until intervention initiation. A blind design (masking both investigators and participants) was implemented, with primary endpoints adjudicated by a blinded endpoint committee.

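### E-values carry no information about robustness for the randomised active-versus-sham comparison and should be confined to analyses that randomisation does not protect

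*Protocol article*

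**What the plan says.** Section 2.11.2 of the protocol article (Control of confounding bias) defines a confounder as a third variable tied to both exposure and outcome. It lists multivariable regression and propensity score matching as controls. It then adds that "sensitivity analyses were conducted to assess potential impacts of unmeasured confounders", with E-values "quantifying the robustness of causal inferences". It names no outcome or comparison for the E-values, sets no threshold, and does not limit them to any type of analysis.

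The neighbouring sections describe a randomised comparison:

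- Section 2.11.3: "This study employed a prospective randomized double-blind RCT design".
- Section 2.11.1: "An independent statistician executed the randomization process to eliminate investigator interference in group assignment", with concealment until enrolment. The design is said to have "ensured balanced distribution of confounding variables across study arms".

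Two other places bear on the point. Under sections 2.6 and 2.7 the sham device touches the ear but delivers no current, and the consent form tells participants that the two interventions may differ in electrical sensation and in response. Section 2.8.3.4 covers an association that is not randomised: "Pearson correlation analysis was performed to assess the association between dynamic changes in neurotransmitter levels and improvement magnitudes of PSQI/NDSI scores".

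**The concern.** An E-value states how strongly an unmeasured common cause of exposure and outcome would have to act to explain away an observed association. When exposure is assigned at random and concealed, no such cause exists except by chance, and the p-value and confidence interval already allow for chance. By the article's own definition of a confounder, the quantity has no target in the active-versus-sham comparison.

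The wording in section 2.11.2 reaches further than confounding, because it ties the E-value to the robustness of causal inference in general. A likelier threat here is that participants notice whether they feel current and rate their symptoms accordingly. Subjective sleep quality is one PSQI component, and the NDSI quantifies symptoms, so both primary scales are open to expectation. The E-value takes the same value whether a difference comes from stimulation or from expectation. At stake is a published figure that looks like support for causality and is not. Meanwhile the association where confounding does arise, between neurotransmitter change and symptom change, has only a plain correlation named for it.

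**Working it through.** **Inputs.** From section 2.5: "anticipated efficacy rates of 20% in the sham stimulation group and 70% in the active stimulation group", α = 0.05, power 0.99, 30 per arm enrolled, anticipated dropout 5–10%. From section 2.8.5: two-sided testing. The article gives no E-value. The standard formula is E = RR + √(RR × (RR − 1)). For a continuous outcome, the usual approximation RR = exp(0.91 × d) is assumed, with d the standardised mean difference.

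**The plan's own figure.** An unpooled two-sided z-test gives [0.2 × 0.8 + 0.7 × 0.3] × (1.960 + 2.326)² / 0.5² = 27.19, so 28 per group. This matches section 2.5, and the design rates are used below.

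**1. The E-value depends on the estimate or its limit alone.**

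- Design rates: RR = 0.70/0.20 = 3.5, so E = 3.5 + √(3.5 × 2.5) = 6.46.
- With 21/30 versus 6/30, the 95% interval for RR is 1.65 to 7.43. The lower limit gives E = 2.68.
- Continuous scale, smallest significant difference at 30 per arm: d = t(0.975, 58) × √(2/30) = 0.517, RR = 1.60, E = 2.58.
- d = 0.8 (an illustrative assumption): RR = 2.07, E = 3.56. The lower 95% limit gives RR = 1.28, E = 1.89.

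Each value is read straight off the estimate or limit and contains nothing further.

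**2. It cannot separate expectation from effect.** Assume no true effect and 20% response in both arms. Let a share q of active-arm non-responders report response because they feel current. The active rate becomes 0.2 + 0.8q.

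| q | active rate | E |
|---|---|---|
| 0.25 | 40% | 3.41 |
| 0.375 | 50% | 4.44 |
| 0.5 | 60% | 5.45 |
| 0.625 | 70% | 6.46 |

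At q = 0.625 the result equals that of a true 70% versus 20% effect. In 100,000 simulated trials of 30 per arm (half an event added to each count), the median E is 6.18 in both cases. They agree by construction, because the E-value sees only the two rates.

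**3. Chance alone.** With 20% in both arms, no effect and no bias, the same simulation gives a median point-estimate E of 2.15. The confidence interval deals with this; a point E-value does not.

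**4. Selective loss at the anticipated dropout.** Assume no effect and a common response rate p. In the worst pattern a fraction l of each arm is lost, all of them non-responders under active and all responders under sham. Then RR = p/(p − l).

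- l = 5%: p = 30% gives RR 1.20, E 1.69; p = 45% gives RR 1.125, E 1.50.
- l = 10%: p = 30% gives RR 1.50, E 2.37; p = 45% gives RR 1.29, E 1.89.
- At the design sham rate p = 20%: l = 5% gives RR 0.20/0.15 = 1.33, E = 1.33 + √(1.33 × 0.33) = 2.00. With l = 10%, RR = 0.20/0.10 = 2, E = 2 + √2 = 3.41, but half of all sham responders must then be lost.
- Even in that last case, 6/27 versus 3/27 has standard error √(1/6 − 1/27 + 1/3 − 1/27) = 0.653 for log RR. The lower limit is exp(0.693 − 1.96 × 0.653) = 0.56, below 1, so the E-value for the limit is 1.

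**The case against.** The best defence is that the E-value is faulted for a job it was not given. Section 2.11.2 directs it at unmeasured confounders. Unblinding has its own measures (masked display, blinding of participant, operator and assessor, blinded adjudication in sections 2.6, 2.11.3 and 2.11.5), and section 2.8.5 handles missing data by multiple imputation with a per-protocol sensitivity analysis. Deleting the E-value would not repair the sham. All of that stands, and the adequacy of the sham is a separate matter. It does not rescue the E-value: for confounding itself, the randomised comparison offers nothing to measure, and the phrase about causal inference is wider than confounding.

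The defence is also right that E-values have a use in this trial. The per-protocol set in section 2.8.5 is selected on events after randomisation, and a propensity-matched subset is no longer the comparison as randomised. A reader might infer that the neurotransmitter correlation is the only place where confounding can arise. The article does not support that, and the fix must leave those other uses open.

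A reader might also infer that the plan would certify the PSQI and NDSI results as causally sound. The article names neither outcome in connection with E-values and sets no cut-off, so a spurious difference would look robust only if it were large. Nor does the article show that the neurotransmitter association will go unadjusted. Section 2.11.2 mentions multivariable regression in general terms, but it does not link that to this association.

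**Conclusion.** The point holds in a limited form. Section 2.11.2 offers E-values as a measure of causal robustness without excluding the comparison as randomised, where they only restate effect size and precision. At the design rates the E-value is 6.46 whether the difference is real or wholly an expectation effect. The second case rests on an assumed 62.5% of active-arm non-responders reporting response; smaller shares give smaller values.

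A reader might go further and conclude that an effect produced by selective loss would be reported as robust. The figures do not support this. At the anticipated 5–10% dropout, the worst pattern gives E of about 1.5 to 2.4 for assumed response rates of 30–45%, against a median of 2.15 from chance alone. At a 20% rate it reaches 3.41 only under an extreme pattern, and the confidence interval still includes no effect.

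The conclusion assumes that allocation is random and concealed. The sections differ on the scheme and the mechanism, but all describe random allocation with concealment. No estimate, interval, p-value or power for the primary test changes. The point is minor and worth making because it is nearly free to correct.

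**What to change.** - **Section 2.11.2.** Drop E-values for the active-versus-sham comparison as randomised, and make no robustness claim from them. If they are kept, restrict them to analyses not protected by randomisation: per-protocol or propensity-matched comparisons and the neurotransmitter–symptom association. Label these as observational.
- **Section 2.8.3.4.** Alongside the Pearson correlation, report the association from a regression of symptom change on neurotransmitter change, adjusted for allocated arm, age, sex and baseline values. Arm belongs in the model because treatment may move both quantities and so create a pooled correlation without any link within arms.

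The cost is a wording change, the loss of one favourable-looking supplementary figure, and one simple regression per analyte and scale on data already collected. With arm, age, sex, two baseline values and the neurotransmitter change, the model has 6 terms for 60 participants, or 54 at 10% dropout. That is 10 or 9 participants per term, enough for a descriptive secondary analysis.
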